| Day 13                  | The study nurse will call to enquire as to adverse effects, pain score and any other problems, and advice on the next dosage. If pain has abated significantly the dose will be left at four tablets at night. If not the dose will be increased to six tablets at night. I                       |
| Week 3 day 15           | The study nurse will call to enquire as to adverse effects, pain score and any other problems, and advise to stay at the same dosage for the next 4 weeks                                                                                                                                         |
| Visit 3.0 Week 3 day 21 | Visit to study site. Check diary, questionnaire administered, medication check, discussion and information as required with participant, reimbursement, referral as required                                                                                                                      |
| Week 4 day 28           | The study nurse will call to enquire as to adverse effects, pain score and any other problems, and advise to stay at the same dosage for the next 3 weeks                                                                                                                                         |

|                         |                                                                                                                                                                                                                                                                                                                                                                                                                                                                                                             |
|-------------------------|-------------------------------------------------------------------------------------------------------------------------------------------------------------------------------------------------------------------------------------------------------------------------------------------------------------------------------------------------------------------------------------------------------------------------------------------------------------------------------------------------------------|

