| Week 5 day 35           | The study nurse will call to enquire as to adverse effects, pain score and any other problems, and advise to stay at the same dosage for the next 2 weeks                                                                                                                                                                                                                                                                                                                                                   |
| Visit 6.0 Week 6 day 42 | 
 
1. Visit to study site Check diary, questionnaire administered, medication check, discussion and information as required with participant, reimbursement, referral as required Collection of demographic data(Appendix I)
 
2. Collection of clinical data(Appendix II)
 
3. Assessment of peripheral neuropathy and other symptoms(Appendix III); if present refer to Palliative care
 
4. Assessment of coexisting pain medication
 
 |
| Week 7 day 49           | The study nurse will call to enquire as to adverse effects, pain score and any other problems                                                                                                                                                                                                                                                                                                                                                                                                               |
| Week 8 day 56           | The study nurse will call to enquire as to adverse effects, pain score and any other problems                                                                                                                                                                                                                                                                                                                                                                                                               |

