| Visit 9.0 Week 9 day 63 | Visit to study site Check diary, questionnaire administered, medication check, discussion and information as required with participant, reimbursement, referral as required. Patient to receive new drug pack                                                                                                                                                                                                                                                                                               |
| Week 10 Day 66          | The study nurse will call to enquire as to adverse effects, pain score and any other problems, and advice on the next dosage. If the pain has abated significantly the dose will be left at one tablet at night. If not, the dose will be increased to two tablets at night for three nights.                                                                                                                                                                                                               |
| Day 69                  | The study nurse will call to enquire as to adverse effects, pain score and any other problems, and advice on the next dosage. If the pain has abated significantly the dose will be left at two tablet at night. If not, the dose will be increased to three tablets at night for three nights.                                                                                                                                                                                                             |

|                                                                   |                                                                                                                                                                                                                                                                                                                                                                                                                                                            |

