| Visit 12.0 Week 12 day 82                                         | 
5. Visit to study site Check diary, questionnaire administered, medication check, discussion and information as required with participant, reimbursement, referral as required Collection of demographic data(Appendix I)
 
6. Collection of clinical data(Appendix II)
 
7. Assessment of peripheral neuropathy and other symptoms(Appendix III); if present refer to Palliative care
 
8. Assessment of coexisting pain medication
 |
| Day 91                                                            | The study nurse will call to enquire as to adverse effects, pain score and any other problems, and advice to stay on the same dosage for the next 2 weeks                                                                                                                                                                                                                                                                                                  |
| Day 98                                                            | The study nurse will call to enquire as to adverse effects, pain score and any other problems, and advice to stay on the same dosage for the next 1 weeks                                                                                                                                                                                                                                                                                                  |
| Exit procedure Week 15 is the exit visit and visit to study site. | Check diary, questionnaire administered, medication check, pain intensity score, clinical examination and discussion and information as required with participant, reimbursement, referral as required. Information on study results feedback session                                                                                                                                                                                                      |

[figure not shown]

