### ***Data collection, management and analysis***

All patients will be allocated a unique identifier that will also serve as their file number on site. All the information for the patient, laboratory results, and questionnaires from different visits, together with the signed informed consent will be kept in the patient's file. The files will be locked up in a cupboard with limited access control.

Double entry of data collected will be entered using Microsoft Access. R statistical package will be used to analyse the data. Descriptive statistics will be used to describe the demographics and clinical characteristics of the population studied.

The primary outcome (pain relief between baseline and end of the study) will be compared for the

- significance of overall pain relief for repeated measures using univariate analysis of variance (ANOVA)
- Association of the drug and the level of pain relief between different subjects using ANOVA.

The number needed to treat (NNT) will be calculated to assess the effectiveness of the drugs, while the number needed to get severe side effects will be calculated as NNF. During analysis subjects will be adjusted according to exposure to neurotoxic drugs. Analysis will also be done using the intention to treat analysis, where all randomised subjects will be included in the analysis to reduce bias.

The number treated analysis will also be done looking only at those subjects who managed to reach the maximum dose of the drugs. This however is subject to selection bias as subjects who developed side effects and those who were lost to follow up will be excluded. The effect of the use of other pain medication in together with the intervention being tested will also be analysed.

The results will be adjusted for ART during analysis, as all patients including those already on ART will be included in the study.

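### The clinical, neuropathy and co-medication block is scheduled at week 6 of period 1 but at about week 3 of period 2, and the week 15 exit row does not name its neuropathy or co-medication items

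*Protocol*

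**What the plan says.** All visit contents are in the Protocol, Study procedures, in the table under the follow-up procedures.

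- **End of period 1.** "Visit 6.0 Week 6 day 42" carries a numbered list of four items: the usual visit checks with demographic data, clinical data (Appendix II), the neuropathy and symptom form (Appendix III), and "Assessment of coexisting pain medication".
- **Middle of period 1.** "Visit 3.0 Week 3 day 21" carries only the usual checks, with none of items 2 to 4.
- **Start of period 2.** "Visit 9.0 Week 9 day 63" is where the new drug pack is handed out.
- **Middle of period 2.** "Visit 12.0 Week 12 day 82" carries the same four items in the same words, numbered 5 to 8 as if continuing the Visit 6.0 list.
- **End of period 2.** "Exit procedure Week 15 is the exit visit and visit to study site". Its content begins "Check diary, questionnaire administered, medication check, pain intensity score, clinical examination" and goes on to discussion, reimbursement and referral. Neither Appendix III nor coexisting pain medication is named.

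The co-medication data have a stated use. The analysis section says: "The effect of the use of other pain medication in together with the intervention being tested will also be analysed". The Ethics review section, in its discussion of placebo control, says that rescue use for neuropathic pain will be recorded and allowed for in the analysis.

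**The concern.** In a two-period crossover, each measure should be taken at the same point in both periods, so that a participant's two readings differ only by treatment and period. Here the block is attached to the last visit of period 1 but to the middle visit of period 2. Followed literally, the schedule gives neuropathy, symptom and co-medication readings after six weeks of treatment in one period and after about three weeks in the other.

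Two things are at stake. First, any treatment contrast on the Appendix II and III data would mix a six-week and a three-week reading and could not be described as either. Second, the named co-medication assessment coincides with the final pain reading in period 1 but precedes it by about three weeks in period 2. If no other form fills that gap, the promised co-medication and rescue analysis rests on unlike information in the two periods. An analysis plan cannot recover data that were not collected.

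**Working it through.** **Inputs** (follow-up table unless stated): period 1 starts on day 0; Visit 3.0 is on day 21; Visit 6.0 on day 42; period 2 starts on day 63; Visit 12.0 is printed as day 82; exit is at week 15. Visit window: 3 days either side (Visit windows section).

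**Step 1: the day labels.** Study day = 7 × week. Weeks 3, 6 and 9 give 21, 42 and 63, as printed. Week 12 gives 84, but 82 is printed, so the label is not reproduced. Week 15 gives 105. The phone calls agree: day 91 plus two more weeks is 105, and day 98 plus one more week is 105.

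**Step 2: time on the period's treatment** = visit day − period start.

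| Visit | Calculation | Period day | Range with window | Block named? |
|---|---|---|---|---|
| 3.0 | 21 − 0 | 21 | 18–24 | No |
| 6.0 | 42 − 0 | 42 | 39–45 | Yes |
| 12.0, as printed | 82 − 63 | 19 | 16–22 | Yes |
| 12.0, if day 84 | 84 − 63 | 21 | 18–24 | Yes |
| Exit | 105 − 63 | 42 | 39–45 | Neuropathy form and co-medication not named |

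Visit 12.0 is therefore the counterpart of Visit 3.0, and exit is the counterpart of Visit 6.0. The block follows neither pairing.

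**Step 3: size of the mismatch.** 42 − 19 = 23 days (42 − 21 = 21 if day 84 is meant). The windows do not overlap: the closest permitted approach is 39 − 22 = 17 days (39 − 24 = 15).

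**Step 4: time since the call that fixes the dose** (day 15 in period 1, day 78 in period 2). Visit 6.0: 42 − 15 = 27 days. Visit 12.0: 82 − 78 = 4 days. Exit: 105 − 78 = 27 days. The block is read well into the stable-dose phase in period 1 and just after titration ends in period 2.

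**Step 5: co-medication against the final pain reading.** Period 1: same visit, 0 days apart. Period 2: 105 − 82 = 23 days apart (105 − 84 = 21).

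**Step 6: the primary outcome.** The Study Summary defines the comparison by pain intensity at the start and end of each six-week period. The exit row names a pain intensity score at period day 42, matching Visit 6.0. The Trial abstract adds a daily diary and pain measurement at all five follow-up visits. Pain therefore has a six-week reading in both periods.

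**The case against.** The strongest reply is that the table rows are not exhaustive. Visit 6.0 names no pain intensity score, although the primary objective needs one there, so pain must be collected through the questionnaire. The exit row also has a questionnaire, a medication check and a clinical examination, which may cover neuropathy and co-medication. The section on measuring pain intensity says that the DN4 and BPNS accompany subsequent scores, and the Ethics review section does not tie recording of rescue use to any visit. The exit forms and the figure after the table are not available here. This stands in part: it cannot be said that the data will be missing at exit. But Visit 6.0 lists the questionnaire and medication check and still names neuropathy and coexisting pain medication separately, so the protocol treats them as different items. The exit row is at best ambiguous.

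A reader might also infer that amitriptyline and placebo are compared at unequal treatment durations, or that the estimated effect is diluted by a calculable amount. The documents support neither reading. Pain has a six-week reading in both periods. The mismatch is between periods, and each treatment is taken in period 1 by one sequence and in period 2 by the other, so it does not systematically favour either. No size can be put on any dilution of the other measures, because the documents give no time course of effect. Nor are the Appendix III form and co-medication among the listed secondary outcomes.

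The two-day slip in the Visit 12.0 label is within the visit window and has no analytic weight of its own.

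**Conclusion.** The point holds as a schedule inconsistency that affects supporting data. The named block falls on period day 42 in period 1 and on period day 19 (or 21) in period 2. The visit that should mirror Visit 6.0 does not name the neuropathy form or coexisting pain medication. These data, including the co-medication data meant for the analysis, are therefore not scheduled at the same treatment duration in both periods. In period 2 the named co-medication assessment comes 23 (or 21) days before the final pain reading.

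The primary comparison, sample size and power are untouched. That the mismatch favours neither treatment assumes sequences of about equal size, which the planned block randomisation should deliver. The practical loss also depends on what the exit forms contain: if they already capture both items, only the table needs correcting.

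**What to change.** - List clinical data, the Appendix III neuropathy and symptom form, and coexisting pain medication by name in the week 15 exit row, either moved from Visit 12.0 or repeated.
- Make Visit 12.0 the counterpart of Visit 3.0, so that Visits 3.0 and 12.0, and Visit 6.0 and exit, match item for item. If the block is to stay at Visit 12.0 as well, add it to Visit 3.0.
- Reconcile the Visit 12.0 label with week 12 = day 84.
- Check that the exit form agrees with the revised row.

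The cost is one edit to the table and the visit forms, and a slightly longer exit visit if the items are repeated. If the block is instead kept at Visit 12.0 and added to Visit 3.0, Visit 3.0 also becomes longer. No extra visit is needed, and no dose or clinical rule changes.

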## **Adverse event guidelines**

Downloaded from <http://www.witshealth.co.za/Portals/0/Ethics/POL-IEC-001.doc>

An adverse event is defined as follows; any untoward medical occurrence that may be present during treatment with a medicine/intervention but which does not necessarily have causal relationship with this treatment.

Adverse drug reaction: a response to a medicine that is noxious and unintended. The causal relationship between the reaction and the intervention may be a reasonable possibility.

Unexpected adverse reaction: one in which the nature, specificity, severity or outcome is not consistent with the product information.

Serious adverse event: an untoward medical occurrence that results in death, is life-threatening, requires patient hospitalisation or prolongation of existing hospitalisation, results in persistent or significant disability/incapacity or is a congenital anomaly /birth defect.

All these shall be reported as per Wits HREC requirements within the expected timeframe and in the correct format.

Unblinding of treatment arms will be done if required.

## **Retention strategies**

Regular conversations will occur with participants on the study, building a rapport with participants. Appointments will be made trying to accommodate scheduled clinic visits. An SMS will be sent if the participant allows to remind them of upcoming appointment. Home visits if consented for will be done to remind those who have not come for their visits within three working days of the missed visit. Regular reports will be provided to the study team in the retention rates and those with missed visits. Reimbursement will be provided for incoming journey the visit before to facilitate travel.

## **Visit windows**

A window period of 3 days will be allowed either side of the appointment date. Patients will be reminded of the upcoming appointment 2 days before.

## **Unscheduled visits, withdrawal from study**

Extra visits will be allowed for adverse event. They will be coded thus; if in week 3, V 3.1. Withdrawal from the study shall be immediately effected on request, a form in reasons for withdrawal shall be filled in and another either allowing or withdrawing permission for utilisation of existing data.

## **Recognition and procedures for non-study symptoms and concerns**

Should the study staff be alerted to concerns and symptoms not related to the study, they will act in the following manner, whilst recognising the importance of maintaining confidentiality as far as in the best interest of the participant:

Life-threatening conditions or other emergencies: provide immediate clinical intervention as best possible, and then refer for emergency admission

Major clinical conditions – written (when appropriate) referral to appropriate services, consider admission

Minor clinical conditions - written (when appropriate) referral to appropriate services

Concerns – referral to appropriate services

### **Protocol violations**

Based on the approved study protocol standard operating procedures will be written and kept in an accessible file, dated and updated for all study staff. Staff will sign off on each relevant SOP. Should any study procedures be violated, the PI will be immediately informed, and a written report submitted to the Wits Ethics committee and the DSMB, within two days. If the situation requires Wits HREC mentioned will be notified immediately. The study staff undertake to run the study to ethical practice, and according to GCP guidelines.

### **Guidelines for introducing amitriptyline**

Patients in this group will be given amitriptyline according to the following protocol. The dose of the drug will not be affected by the weight of the patient.

| Dose                                                                 | Days   |
|----------------------------------------------------------------------|--------|
| 25mg od at night
increase the dose on next visit if pain persists | Day 0  |
| 50mg od at night
increase the dose on next visit if pain persist  | Day 3  |
| 75mg od at night
increase the dose on next visit if pain persist  | Day 7  |
| 100mg od at night                                                    | day 11 |
| 150 mg od at night                                                   | Day 15 |

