### ***Follow up procedures: Day 4-day 15***

At home: one tablet will be taken at night for three nights. On the third day the study nurse will call to enquire as to adverse effects, pain score and any other problems, and advice on the next dosage. If the pain has abated significantly the dose will be left at one tablet at

night. If not, the dose will be increased to two tablets at night for three nights. The same procedure will occur until a maximum of 6 tablets at night has been reached. The participant will continue to take this dose for 4 weeks. A weekly telephone call will be conducted by the study nurse.

|                         |                                                                                                                                                                                                                                                                                                   |
|-------------------------|---------------------------------------------------------------------------------------------------------------------------------------------------------------------------------------------------------------------------------------------------------------------------------------------------|
| Day 3                   | The study nurse will call to enquire as to adverse effects, pain score and any other problems, and advice on the next dosage. If the pain has abated significantly the dose will be left at one tablet at night. If not, the dose will be increased by two tablets at night for three nights.     |
| Day 7                   | The study nurse will call to enquire as to adverse effects, pain score and any other problems, and advice on the next dosage. If the pain has abated significantly the dose will be left at two tablets at night. If not, the dose will be increased to three tablets at night for three nights.  |
| Day 11                  | The study nurse will call to enquire as to adverse effects, pain score and any other problems, and advice on the next dosage. If the pain has abated significantly the dose will be left at three tablets at night. If not, the dose will be increased to four tablets at night for three nights. |

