|-------------------------------------------------------------------|------------------------------------------------------------------------------------------------------------------------------------------------------------------------------------------------------------------------------------------------------------------------------------------------------------------------------------------------------------------------------------------------------------------------------------------------------------|
| Week 11 day 72                                                    | The study nurse will call to enquire as to adverse effects, pain score and any other problems, and advice on the next dosage. If the pain has abated significantly the dose will be left at three tablets at night. If not, the dose will be increased to four tablets at night for three nights.                                                                                                                                                          |
| Day 75                                                            | The study nurse will call to enquire as to adverse effects, pain score and any other problems, If not, the dose will be increased to six tablets at night.                                                                                                                                                                                                                                                                                                 |
| Day 78                                                            | The study nurse will call to enquire as to adverse effects, pain score and any other problems, and advice to stay on the same dosage for the next 4 weeks.                                                                                                                                                                                                                                                                                                 |

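### Several dosing instructions do not match the protocol's own titrate-to-effect rule and need an editorial correction

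*Protocol*

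**What the plan says.** The general rule appears in three places. The Trial abstract titrates to effect or to a maximum dose in both periods. The section on amitriptyline for HIV related DSN gives the ladder 25, 50, 75, 100 and 150 mg, titrated to effect. The narrative under Follow up procedures has the nurse hold the dose if pain has abated significantly and otherwise raise it to two tablets, and adds: "The same procedure will occur until a maximum of 6 tablets at night has been reached".

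The detailed instructions then read as follows.

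- Period 1, Day 3 call: "If not, the dose will be increased by two tablets at night for three nights".
- Period 1, Day 11 call, if pain has not abated: "the dose will be increased to four tablets at night for three nights". The next step is the Day 13 call.
- Period 1, Day 13 call: "If pain has abated significantly the dose will be left at four tablets at night"; otherwise six tablets.
- Period 1, Day 15 call: "advise to stay at the same dosage for the next 4 weeks".
- Period 2, Day 75 call, the counterpart of Day 13: "any other problems, If not, the dose will be increased to six tablets at night".
- Guidelines for introducing amitriptyline: a table opening with "Patients in this group will be given amitriptyline according to the following protocol". The 25 mg row says "increase the dose on next visit if pain persists", and the 50 and 75 mg rows say the same in substance. The rows for 100 mg (day 11) and 150 mg (Day 15) give only the dose.

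Neither section says which governs where the two differ.

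**The concern.** These are the instructions that a nurse follows on the telephone, not background text. If one row is followed as printed, a participant can skip the 50 mg step (Day 3), or be raised from 100 to 150 mg without the check for response (Day 75).

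Three things depend on the dose reached: the participant's exposure, the secondary outcomes of minimum efficacious and maximal tolerated dose, and membership of the planned analysis of those who reached the maximum dose. Someone raised without the hold check would enter that subset because of wording, not because of lack of response.

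The Protocol violations section bases the operating procedures on the approved protocol and has violations reported to the ethics committee and the DSMB within two days. Conflicting schedules blur what counts as a violation.

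**Working it through.** **Inputs.** Six tablets are 150 mg, so one tablet is 150 / 6 = 25 mg. Each period has 42 nights. Period 2 starts with the new drug pack on Day 63.

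**Day 3.** As printed, 1 + 2 = 3 tablets, or 75 mg. The narrative and the Day 66 row (66 − 63 = 3, the same point in period 2) both say *to* two tablets, or 50 mg. The Day 7 row assumes two, because it offers a hold at two or an increase to three. A participant on three tablets fits neither branch. From Day 3 to Day 7 the excess would be 4 nights × 25 mg = 100 mg.

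**Day 75.** The row contains an *if not* with no condition before it. The Day 13 row supplies the missing sentence for period 1.

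**Guideline table.** The step from 75 to 100 mg is conditional through the 75 mg row, and 150 mg is the ceiling and needs no hold. The gap is therefore the single step from 100 to 150 mg. The table puts 150 mg at Day 15, when the call schedule says to stay on the same dose. It refers to the next visit, but the first site visit after baseline is Day 21.

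**Step days, counted from the start of each period.**

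| Step to | Period 1 calls | Period 2 calls | Guideline table |
|---|---|---|---|
| 50 mg | 3 | 66 − 63 = 3 | 3 |
| 75 mg | 7 | 69 − 63 = 6 | 7 |
| 100 mg | 11 | 72 − 63 = 9 | 11 |
| 150 mg | 13 | 75 − 63 = 12 | 15 |
| Nights at 25/50/75/100 mg | 3/4/4/2 | 3/3/3/3 | 3/4/4/4 |

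The call rows state three nights per step. Only period 2 delivers that throughout. In period 1 the Day 11 step lasts 13 − 11 = 2 nights.

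**Cumulative dose over 42 nights, participant escalated fully.**

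- Period 1: 25×3 + 50×4 + 75×4 + 100×2 + 150×29 = 5,125 mg
- Period 2: 25×3 + 50×3 + 75×3 + 100×3 + 150×30 = 5,250 mg
- Guideline table: 25×3 + 50×4 + 75×4 + 100×4 + 150×27 = 5,025 mg
- Largest gap: (5,250 − 5,025) / 5,025 = 4.5%

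**Stay-on-dose wording.** The Day 28 row says three more weeks (28 + 21 = Day 49) and the Day 35 row two more (35 + 14 = Day 49), but period 1 ends at Day 42. The counterparts in period 2 are right: Day 91 + 14 = 105 and Day 98 + 7 = 105, which is 63 + 42. The correct durations are (42 − 28) / 7 = 2 weeks and (42 − 35) / 7 = 1 week.

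**The case against.** The strongest reply is that no careful reader would be misled. The rule is stated three times. The Day 3 slip is corrected by the narrative directly above it and by the Day 7 and Day 66 rows. The *if not* at Day 75 presupposes the missing condition. The timing differences are immaterial. Most of this stands, and it is why the point is minor.

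A reader might infer more in three respects.

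- *That the guideline table sends a participant who has responded on 100 mg up to 150 mg.* On that reading the participant would take 5,025 mg, against 25×3 + 50×4 + 75×4 + 100×31 = 3,675 mg if held, a difference of 27 × 50 = 1,350 mg. The table does not say this. At 100 mg it is silent, neither holding nor raising the dose, and the general rule and the Day 13 row fill the silence with a hold.
- *That the unequal schedules bias the treatment comparison.* They do not invalidate it, because both sequences pass through both periods.
- *That days 3/6/9/12 are the only correct ones.* They fit the stated three nights, but period 1 and the table agree on 3/7/11, so a slower common schedule is also defensible.

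What remains is that operative dosing rows contradict each other, and that a recoverable intent makes them easy to correct.

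**Conclusion.** The point holds as a minor editorial defect in operative text. Four things depart from the titrate-to-effect rule or from each other: the Day 3 wording, the missing hold at Day 75, the unconditioned 100 to 150 mg step with its Day 15 timing and its reference to visits, and the three sets of step days. The stay-on-dose durations at Days 28 and 35 are also a week too long.

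The randomised primary comparison is not invalidated, and timing alone shifts cumulative dose by at most about 4.5% for a participant who escalates fully. The possible effect is on individual exposure, the two dose-finding secondary outcomes and the maximum-dose subset. How many participants would be affected is unknown, and the protocol gives no figure from which to estimate it. The arithmetic assumes 25 mg tablets, a first dose on the first night of each period, and dosing for 42 nights.

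**What to change.** 1. Replace the table under Guidelines for introducing amitriptyline with a reference to the telephone schedule under Follow up procedures, for both periods.
2. In the Day 3 row, change *by* two tablets to *to* two tablets.
3. In the Day 75 row, insert before the *if not* the sentence used at Day 13: "If pain has abated significantly the dose will be left at four tablets at night".
4. Use one set of step days in both periods. Days 3/6/9/12 match the stated three nights; in period 1 the calls on Days 7, 11 and 13 would move to 6, 9 and 12. If slower escalation is preferred, use a slower common schedule and change the three-nights wording to match.
5. Correct the stay-on-dose advice to two weeks at Day 28 and one week at Day 35, so that period 1 dosing ends at Day 42.

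The cost is text only. With days 3/6/9/12, three period 1 calls move by one or two days. No calls, visits or data are added.
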